## Source of subjects and recruitment methods

Subjects are eligible if presenting from 4 settings, as outlined above (“location of presentation”):

- Emergency departments at BWH and BWFH
- Inpatient wards at BWH and BWFH

- Patient homes of previously home hospitalized patients
- BWH and BWFH clinics
- Those meeting primary diagnosis, age, and geographic requirements will be screened by our research assistants for further enrollment (below).

## Subject Enrollment

### Methods of enrollment, Procedures for obtaining consent

- Decision to admit or observe made by emergency room team or by an ambulatory clinician who would otherwise admit her/his patient.
- Participant is pre-screened by a research assistant for primary diagnosis, age, and residence within 7.5 miles via the electronic medical record.
- If participant meets those criteria, the emergency room team or ambulatory clinician will ask the patient/caregiver if the research assistant can approach the patient regarding the home hospital study.
- If participant agrees, the research assistant will describe the program, answer initial questions, and further assess whether the participant meets inclusion/exclusion non-clinical (e.g., social) criteria. The RA will then contact the on-call MD to assess clinical criteria by EHR review.
- If the participant has interest in the program and meets inclusion/exclusion criteria, the on-call MD (either in-person or via a live video visit facilitated by the research assistant) will obtain written informed consent of the participant to enroll in the home hospital program.
- For a subject known to be without capacity, any of the following individuals (listed in general order of preference) may give consent provided they are on-site and able to sign the informed consent (the patient will assent):
  - court appointed guardian with specific authority to consent to participation in research or authority to make health care decisions for a class of diagnostic and therapeutic decisions inclusive of the proposed research;
  - health care proxy/person with durable power of attorney with specific authority for making health care decisions inclusive of the proposed research; or
  - spouse, adult child, or other close family member who knows the subject well and has been involved in their care.
  - When surrogate consent is relied upon, the Investigator must ensure that the surrogate understands that his or her decisions should be based on "substituted judgment." This means that the decision reflects a potential subject's own views when s/he had the capacity to express them. If a potential subject did not previously express a view on the matter, the surrogate should make the decision based on the potential subject's best interests.
  - When surrogate consent is relied upon, assent of the subject will be a requirement for participation in the research unless the subject is incapable of giving assent due to his/her medical condition. If the individual objects to participation, s/he will not be enrolled.
  - In the case of surrogate consent, a patient must be returning to their prior level of supervision.
- For patients already on the hospital floor: Previously, we had only allowed patients who had been admitted for less than 24 hours to be home hospitalized. We now wish to expand this criterion to patients at any timepoint in their hospitalization. We believe that many patients may benefit from home hospital care, irrespective of how long they have been traditionally

hospitalized. Enrollment will proceed exactly as in the emergency department, with the exception that it will need to be assessed and reassessed daily with an inpatient team to determine the time at which the patient has a stable acute care plan that meets all of the above criteria. That is, the patient is clinically improving, has continued low probability of clinical deterioration or need for an invasive procedure, but still requires acute care.

- Subjects who do not speak English will use a short-form consent form with the assistance of a certified telephone interpreter.

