- Regarding exacerbation of cystic fibrosis or non-cystic fibrosis bronchiectasis
  - Exacerbation ( $\geq 4/12$ )
    - Change in sputum
    - New or increased hemoptysis
    - Increased cough
    - Increased dyspnea
    - Malaise, fatigue or lethargy
    - Temperature above 38°C
    - Anorexia or weight loss
    - Sinus pain or tenderness
    - Change in sinus discharge
    - Change in physical examination of the chest;
    - Decrease in pulmonary function by 10 percent or more from a previously recorded value
    - Radiographic changes indicative of pulmonary infection
- Location of presentation
  - Emergency department
    - Decision to admit or observe patient made by emergency department
  - Hospital floor
    - Patient is clinically stable with a clear plan for continued acute care, as agreed upon by the inpatient and home hospital teams
    - All inclusion and exclusion criteria must still be fulfilled
  - Home
    - Patient is known to the home hospital team from a prior home hospitalization
    - All inclusion and exclusion criteria must still be fulfilled. This requires the same clinically warranted workup as the patient would have received in the emergency department or upon arrival to the floor, including imaging and other diagnostics. Should these be warranted and not be available (e.g., expedited CT imaging), the patient would be excluded.
  - Clinic
    - Patient is well-known by a referring clinician who is confident of the diagnosis and management after a history, physical, and if warranted diagnostic testing in the clinic. For example, a cardiologist might refer a patient with known heart failure from clinic who has volume overload and would otherwise directly admit her/his patient to the floor.
    - All inclusion and exclusion criteria must still be fulfilled. This requires the same clinically warranted workup as the patient would have received in the emergency department or upon arrival to the floor, including imaging and other diagnostics. Should these be warranted and not be available (e.g., expedited formal TTE), the patient would be excluded.

*Exclusion*

- Social
  - Undomiciled
  - No working heat (October-April), no working air conditioning if forecast > 80°F (June-September), or no running water
  - On methadone requiring daily pickup of medication
  - In police custody
  - Resides in facility that provides on-site medical care (e.g., skilled nursing facility)
  - Domestic violence screen positive
- Clinical

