## Statistical methods

### *Home hospital vs traditional hospital*

#### *Quantitative*

We plan to form 3 different control groups (with groups listed in order of preference):

1. Patients who were deemed eligible for home hospital, but the service was full (and they were not enrolled subsequently if the service was no longer full);
2. Patients who were deemed eligible for home hospital, but lived outside of the 7.5-mile catchment area; and
3. Patients who were admitted to the hospital.

For each control group, we will use propensity score weighting, adjusting for covariates of interest (see table above), baseline functional status, and DRG. We will be cognizant of over-adjustment depending on our final sample size for each group above. If possible, we will use only group 1 above, as it is the strongest. If we have insufficient control group sample size, we may choose to combine groups 1 and 2 above.

The primary outcome (hospitalization cost) will be assessed using a generalized linear model assuming a gamma distribution with a log link. We will use a multivariable regression approach for secondary

outcomes, using logistic regression for binary outcomes and non-transformed linear regression for normally distributed continuous outcomes as appropriate.

We *a priori* plan to perform a subgroup analysis that does not involve any outlier participants, should this occur. We also *a priori* plan subgroup analyses by diagnosis, by age group, by disposition, by location of admission (e.g., ED, floor, clinic, and home), and by daily activity level. We also *a priori* plan to analyze our outcomes with means, but also with median and interquartile ranges, which are less subject to outlier effects. We may choose to employ non-parametric tests of significance should our data be nonparametric.

We *a priori* plan to adjust our secondary analyses using the Benjamini-Hochberg method. We *a priori* choose a false-discovery rate of 0.20.

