#### ***Early transfer to home hospital vs traditional hospital***

We plan to use the same statistical analysis as in the Standard Home Hospitalization methods noted above. However, we do anticipate requiring an additional variable that notes whether a patient was initially considered for home hospital care and was not eligible due to a full census, and then was later taken home when the home hospital service census allowed.

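### The early-transfer comparison does not account for hospital day or clinical status at the transfer decision, so selection on in-hospital course may bias it

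*Protocol*

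**What the plan says.** **Who is transferred, and when.** The protocol's enrollment section widens ward transfer from the first 24 hours: "We now wish to expand this criterion to patients at any timepoint in their hospitalization". Each ward patient is "assessed and reassessed daily with an inpatient team to determine the time at which the patient has a stable acute care plan", and that point is described as one where "the patient is clinically improving, has continued low probability of clinical deterioration or need for an invasive procedure, but still requires acute care". The inclusion criteria for the hospital floor add: "Patient is clinically stable with a clear plan for continued acute care, as agreed upon by the inpatient and home hospital teams".

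**How the comparison is analysed.** Under Early transfer to home hospital vs traditional hospital: "We plan to use the same statistical analysis as in the Standard Home Hospitalization methods noted above". The one addition is "an additional variable that notes whether a patient was initially considered for home hospital care and was not eligible due to a full census". In the standard method, "we will use propensity score weighting, adjusting for covariates of interest (see table above), baseline functional status, and DRG".

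**What the covariates table holds.** Almost every entry is taken at admission, including the InterQual level. The exceptions are the HOSPITAL score, taken at discharge, and a second caregiver-burden reading at day +30.

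**Who the controls are.** Three groups are ranked:
1. eligible patients for whom the service was full and who were not enrolled later;
2. eligible patients living outside the catchment area;
3. patients admitted to the hospital.

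Group 1 alone is to be used if possible, and groups 1 and 2 may be combined if numbers are short.

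**Endpoints and size.** The primary early-transfer endpoint is cost of the acute episode plus 30 days. Unplanned readmission is secondary, and so is the number of adverse events, which is tested for non-inferiority. The power section gives 324 patients per arm and 82% power for a 21% cost reduction.

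**The concern.** Treatment in this non-randomised comparison is assigned on how the patient has done since admission. Two clinical teams look each day for improvement and a low chance of deterioration, and these are predictors of the outcomes being compared. Weighting can balance only what it contains. Two patients with the same age, comorbidities, functional status and DRG may be on quite different courses on hospital day 3, and the planned model cannot tell them apart.

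The choice of controls does not clearly repair this. Eligibility in groups 1 and 2 is not tied to a hospital day, and group 3 carries no stability condition. Group 1 also conditions on the future: a waiting patient who improves, still needs acute care and gets a place leaves the control pool for the home arm.

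At stake are the cost result, the readmission result and the adverse-event non-inferiority claim for early transfer. Floor-origin patients also enter the main home-versus-hospital comparison, where location of admission appears only as a subgroup.

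**Working it through.** **1. The plan's own figure.** From the Early Transfer power paragraph: 324 per arm, intraclass correlation 0.01, cluster size 65, cost ratio 0.79, power 82%. The protocol gives no coefficient of variation (CV) for cost and no alpha for this comparison. I assume 0.05 two-sided.

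- Design effect = 1 + (65 − 1) × 0.01 = 1.64, so the effective n is 324 / 1.64 = 197.6 per arm.
- Power = Φ(|ln 0.79| / (CV × √(2/197.6)) − 1.96).
- This gives 97% at CV 0.6, 83% at 0.8, 65% at 1.0 and 50% at 1.2.

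The 82% cannot be reproduced without a CV. Solving backwards, it implies a CV of about 0.815, that is, a standard error of the log cost ratio of 0.2357 / (1.960 + 0.915) = 0.082. Nothing here shows the stated power to be wrong; the implied CV is needed only for step 3.

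**2. Size of the selection effect when there is no true effect.** Let p be the share of weighted controls who are improving and r the proportion by which improving patients cost less than the others. All transferred patients are improving by rule. The apparent saving is

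1 − (1 − r) / (p(1 − r) + 1 − p) = 1 − (1 − r) / (1 − pr).

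Example: p = 0.5, r = 0.2 gives 1 − 0.80/0.90 = 11.1%.

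| Share of controls improving (p) | r = 10% | r = 20% | r = 30% | r needed for a false 21% |
|---|---|---|---|---|
| 30% | 7.2% | 14.9% | 23.1% | 27.5% |
| 50% | 5.3% | 11.1% | 17.6% | 34.7% |
| 70% | 3.2% | 7.0% | 11.4% | 47.0% |
| 90% | 1.1% | 2.4% | 4.1% | 72.7% |

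The last column is 1 − 0.79(1 − p)/(1 − 0.79p). Neither p nor r is in the protocol. I read the 30% and 50% rows as controls like group 3, and the 90% row as controls like group 1 whose eligibility did mean floor eligibility at a comparable time.

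**3. What such a bias does to the test.** With the standard error of 0.082, the chance of a significant saving under no true effect is Φ(−ln(1 − bias)/0.082 − 1.96), against a nominal 2.5%:

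| Bias | Chance of a significant saving |
|---|---|
| 1.1% | 3% |
| 4.1% | 7% |
| 5% | 9% |
| 10% | 25% |
| 15% | 51% |
| 20% | 78% |

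**4. Whether matching on the criterion removes it.** In an illustrative null simulation of full-episode cost, weights used one admission covariate only, and the slowest 16% never became improving wherever course varied. As the SD of the unmeasured course (log scale) went through 0, 0.2, 0.4 and 0.6, the apparent cost ratio was 1.00, 0.93, 0.86 and 0.77. When controls also had to reach the improving state, the ratio was 0.999 to 1.006 throughout. This shows the mechanism and the remedy, not the size to expect in this trial.

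**The case against.** The strongest reply is the ranking of control groups. Groups 1 and 2 were judged eligible, which for a ward patient includes stability agreed by both teams. The plan prefers group 1 alone, and its named fallback adds group 2, so the unscreened group 3 is the last choice. This largely stands. It means the upper part of the range applies to group 3, and that a well-defined group 1 would bring the bias down to the 90% row. It does not close the point, because eligibility has no date and group 1 removes patients enrolled later.

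Several stronger readings are tempting, and the documents do not support them:

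- **That all three endpoints are biased in favour of home.** The rule also requires that the patient still needs acute care. Patients who recover and are discharged before they could be transferred stay among the controls and pull the other way. Nor does the protocol say whether ward cost before transfer counts in a transferred patient's episode.
- **That no control need meet the transfer rule.** This is true of group 3 only.
- **That the weighting set holds admission data only.** It also has DRG, the census variable and the discharge HOSPITAL score. None measures recovery at transfer, and a discharge score comes after treatment has started.
- **That functional status is recorded mid-recovery in transferred patients.** The protocol does not say so, and ADL, IADL and SF-1 are also collected for day −30.

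A last reply is that index dates and final propensity variables belong in the SAP. That is often so, but here the protocol itself names the weighting set, the control groups and the single addition for early transfer.

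**Conclusion.** The concern holds as a risk of confounding. As written, the early-transfer analysis adjusts for nothing that records hospital day or clinical status when the transfer decision is made, and it compares transferred patients with controls who have no corresponding index day. The likely direction favours home, without certainty.

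The size cannot be derived from the protocol. It is about 5% to 23% of cost if 30% to 50% of controls are improving, and about 1% to 4% if 90% are, in each case with improving patients costing 10% to 30% less. The formula treats cost from the index day onward. If pre-transfer ward cost is counted in both groups, the percentages are diluted. Selection alone matches the 21% design effect only at the extreme of this range, but a smaller bias can still produce a significant result or inflate a real saving. The change should be made before the comparison is run.

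**What to change.** Leave the transfer criterion as it is and change the analysis:

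- For floor-origin patients, set the index time at the transfer-decision day.
- Use as controls patients still in hospital on the same hospital day who meet the plan's existing floor-eligibility criteria on that day, as judged from the electronic record.
- Add hospital day and that day's status (vital signs, oxygen, IV therapy, laboratory values) to the propensity model.
- Count cost and events from that index day in both groups, and say so in the endpoint definition.
- In the main home-versus-hospital model, weight floor-origin patients within their own stratum.

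The cost is record abstraction for controls and fewer usable controls, hence some loss of precision. Daily IV medication, oxygen and laboratory orders are already on the protocol's data-collection list, so part of the material should exist. Enrollment and care do not change.

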## Treatment Assignment

- All patients will be offered home hospitalization.
- If patient/caregiver does not consent, the research assistant will ask the patient's permission to collect covariates, functional status, and a quality of life measure to determine generalizability of enrollment.

As an amendment to our current protocol, patients will be randomized (random sized blocks between 3 and 6 stratified by infection, heart failure, COPD/asthma, and other with concealed allocation) to remote care (intervention) versus in-person care (control) at the time of enrollment. Once 210 patients have been enrolled in this schema (see power calculations below), and if remote care is noninferior to in-person care, we will allow remote care to continue as a single arm while continuing other concurrent experiments.

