### *Remote vs In-Person Care Analysis*

During our prior RCT of home hospital, patients experienced a mean of 0.09 (SD 0.29) adverse events during their home hospital admission. We believe the smallest clinically meaningful treatment difference would be 0.1 adverse events (i.e., from 0.09 to 0.19 adverse events per patient). In this non-inferiority trial ( $\alpha=0.025$ , power 80%, non-inferiority limit 0.1 events), we would require 210 patients (105 in each arm). Because of clustering, the actual required sample size will be larger. With 5 home hospital physicians ( $\rho$  0.01), we require 260 patients (130 in each arm). We consistently enroll 25 patients monthly, leaving us with sufficient power after about 11 months.

We plan an interim futility analysis. After 130 patients have completed the remote vs in-person care study, we will calculate the difference in adverse event rates between the two arms. If the difference is 0.10 or higher (with the higher rate in the intervention arm), then we will stop the trial for futility. This rule will reduce the power about 2%.

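### The remote-care decision is triggered at 210 enrolled patients, the figure before clustering, although the protocol's own power section requires 260

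*Protocol*

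**What the plan says.** Treatment Assignment sets the rule: "Once 210 patients have been enrolled in this schema (see power calculations below), and if remote care is noninferior to in-person care", then "we will allow remote care to continue as a single arm while continuing other concurrent experiments". This is the only place where the protocol says when non-inferiority is judged and when randomisation gives way to one arm.

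The cross-reference leads to Power analysis, Remote vs In-Person Care Analysis. Its inputs are a prior result in which "patients experienced a mean of 0.09 (SD 0.29) adverse events during their home hospital admission", an alpha of 0.025, and "power 80%, non-inferiority limit 0.1 events". They lead to 210 patients, 105 per arm. The section then sets that figure aside: "Because of clustering, the actual required sample size will be larger". With five physicians and an intraclass correlation of 0.01, "we require 260 patients (130 in each arm"). It expects sufficient power after about 11 months at 25 patients a month, and places a futility look after 130 patients have completed.

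Statistical methods, Remote vs In-Person Physician Care, commits the primary analysis to clustering by physician with estimating equations.

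**The concern.** The decision rule uses a sample size that the section it cites has already replaced. Everything else in the plan follows 260. The futility look at 130 is half of 260. At 25 patients a month, 260 takes 10.4 months, close to the stated 11, while 210 takes 8.4. The primary analysis also allows for the clustering that the figure of 210 ignores.

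Staff who follow Treatment Assignment would judge non-inferiority 50 patients short of the planned size. A remote model that is truly no worse could then fail its test for want of patients the plan has already budgeted. The protocol also does not say what happens if non-inferiority is not shown at 210.

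**Working it through.** **Inputs (Power analysis, Remote vs In-Person Care Analysis).** Margin 0.1 events; SD 0.29; true difference taken as 0; power 80%; stated alpha 0.025, taken as one-sided because the protocol does not give the sidedness; five physicians; intraclass correlation 0.01.

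**Step 1: reproduce 210.** Per arm, n = 2 × SD² × (z for alpha + z for power)² / margin².
- One-sided 0.05: 2 × 0.0841 × (1.645 + 0.842)² / 0.01 = 104.0. The t-test version gives 105, hence 210 in total. This matches the plan.
- One-sided 0.025: 2 × 0.0841 × (1.960 + 0.842)² / 0.01 = 132.0, rounded up to 133, hence 266. This does not match.

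So the plan's figures correspond to one-sided 0.05, not to the stated 0.025.

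**Step 2: reproduce 260.** Design effect = 1 + (m − 1) × 0.01, where m is patients per physician per arm. With m = 130/5 = 26 the design effect is 1.25, and 104 × 1.25 = 130 per arm, or 260. The step from 210 to 260 reproduces.

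**Step 3: power at each size.** Effective n = n / design effect. Power = Φ[0.1 / (0.29 × √(2 / effective n)) − z for alpha].

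| Total | m | Design effect | Effective n per arm | Power, one-sided 0.05 | Power, alpha 0.025 |
|---|---|---|---|---|---|
| 210 | 21 | 1.20 | 87.5 | 73.8% | 62.6% |
| 260 | 26 | 1.25 | 104.0 | 80.0% | 70.1% |

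For 210 the first term is 0.1 / (0.29 × √(2/87.5)) = 2.281. Subtracting 1.645 gives 0.636 (73.8%), and subtracting 1.960 gives 0.321 (62.6%). For 260 it is 2.487, which gives 0.842 (80.0%) and 0.527 (70.1%).

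The loss from using 210 in place of 260 is therefore 80.0 − 73.8 = 6.2 points, or 70.1 − 62.6 = 7.5 points.

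**Step 4: size that gives 80% at alpha 0.025.** Solving n = 132.0 × [1 + (n/5 − 1) × 0.01] gives n = 132.0 × 0.99 / (1 − 132.0 × 0.01/5) = 177.6, that is 178 per arm or 356 in total.

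**Step 5: if the test were run at 210 and again at 260.** The two statistics have correlation √(210/260) = 0.899. The chance that at least one passes the one-sided 0.025 limit when remote care is worse by exactly the margin is 3.5%.

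**The case against.** - **False adoption.** A reader might infer that deciding at 210 makes it easier to adopt an unsafe model. The document does not support that. The switch requires non-inferiority to be shown, and a smaller sample in one valid test makes that harder to show.
- **Inflated error.** A reader might also take the 3.5% as a property of the plan. No section plans a second test, and the only stated interim look is for futility. The figure applies only if the test is repeated at 260, a course on which the protocol is silent.
- **Size of the loss.** It would be wrong to blame the whole gap between 80% and 63% on the 210. Only 6 to 7.5 points come from it. The rest comes from a separate mismatch between the stated alpha and the alpha that reproduces the sample sizes.
- **Clustering assumption.** The power figures depend on how physicians relate to arms, which is not stated. If each physician treats both arms and the physician effect is common to them, most of it cancels, and 210 gives about 81% at one-sided 0.05. If instead the penalty is applied to each physician's patients across both arms, 210 gives 67.7% at one-sided 0.05 and 55.7% at 0.025. This stands as a limit on the exact figures. It does not remove the contradiction, because the plan chose the penalty that leads to 260.
- **A stale number.** The 210 may simply be left over, since accrual and the futility look follow 260. That is plausible, but the stale number sits in the operative rule.

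**Conclusion.** The contradiction stands. The rule for judging non-inferiority and moving to a single arm uses 210, while the power section requires 260, and nothing in the protocol reconciles them. On the plan's own clustering assumption (intraclass correlation 0.01, five physicians, 21 patients per physician per arm), deciding at 210 gives about 74% power instead of 80% at one-sided 0.05, or about 63% instead of 70% at the stated 0.025. The consequence is a greater risk of an inconclusive trial. The type I error of a single test is unaffected.

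Moving to 260 removes the contradiction but does not deliver 80% power at the stated alpha.

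**What to change.** 1. In Treatment Assignment, replace 210 with the clustered target in the power section, 260 (130 per arm).
2. State that non-inferiority is tested once, after those randomised patients have complete primary-outcome data, and that the futility look at 130 is the only earlier look. Complete must be defined: Statistical methods limits the primary outcome to events in the acute episode, but the Summarizing Adverse Events table it points to includes unplanned 30-day post-discharge mortality. The two need to be reconciled first, because they imply different cut-off dates.
3. Beside the 260, correct either the alpha (the figure matches one-sided 0.05) or the power (about 70% at 0.025). Keeping both 0.025 and 80% would need about 356 patients under the plan's clustering assumption.

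Items 1 and 2 are short text corrections and need no patients beyond the 260 already planned. Item 3 is also only text, unless the sponsor chooses to keep both the alpha and the power. That choice adds about 96 patients (356 − 260), a little under four months at 25 a month.
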